### Trial arms

Eligibility screening and randomization to trial arms will occur on a rolling basis, aligned with designated recruitment periods in the fall, spring, and summer semesters. All PA sessions will be delivered by trained Sport and Recreation PA coaches at the University of Toronto. Following group allocation to an intervention arm (1:1 or group-based PA), students will be matched with a coach and work with the same coach throughout the duration of the 6-week program. All PA sessions for the intervention arm are expected to commence within one week of randomization. Students assigned to 1:1 delivery will be matched immediately with a PA coach to coordinate weekly sessions. Group-based PA sessions will start once 3–8 students have been allocated and will be scheduled at a time that works for most students enrolled. Modifications to the allocated trial arm (e.g., switching from group to 1:1 PA delivery or from the control arm to an intervention arm) will not be permitted within the research protocol. However, students who are unable to follow through with their assigned trial arm will be offered PA sessions outside of the research (1:1 or group-based, depending on student preference) as part of standard service provision. Reasons for not initiating an assigned trial arm will be documented as part of the mixed methods process evaluation, as an indicator of adherence to the trial. To improve adherence to the intervention protocol by students, coaches will be in contact with students weekly to schedule sessions and will send reminder emails to students about upcoming sessions. To improve adherence to the intervention protocol by coaches, a standardized behavior change coaching booklet will be used to guide all PA intervention sessions. Regular bi-weekly check-ins with PA coaches and the research team will be conducted to support consistent delivery and to monitor implementation and student progression through the PA intervention. In addition, fidelity to core intervention processes will be examined based on student-reported experiences (see Implementation Process Evaluation Outcomes). Concomitant mental health care (e.g., therapy, medication use) and engagement in additional on-campus resources will be permitted during the trial and reported on to describe the student sample.

### Intervention arms

The intervention arms are grounded in behavior change theory and empirical evidence on PA for mental health [14,25,38,39], with sessions designed to meet students’ PA related needs and preferences. To support student preferences, PA sessions will be delivered in-person in private PA spaces in the Mental Health and Physical Activity Research Center, located in the campus athletics and recreation centre. Public gym spaces will also be used depending on student preferences and interests. While bias related to coaching variability and differences in PA delivery space is plausible, the intervention was intentionally designed using pragmatic principles to reflect real-world conditions [40]. This includes allowing flexibility in implementation, such as permitting coaches with diverse backgrounds to deliver the sessions and enabling students to select preference-based PA delivery space. The purpose is to facilitate enjoyment and key COM-B behavioral processes (capability, opportunity, and motivation), to support ongoing engagement in PA as a mental health management strategy (see Table 1). Indeed, the COM-B model posits that no behavior will occur without sufficient capability, opportunity, and motivation [43]. The mixed methods process evaluation was designed to assess whether core intervention processes are received by students including acceptability (e.g., enjoyment), student-reported experiences of COM-B processes, and the quality of the coach-student relationship, a core component intended to foster a supportive and collaborative environment.

**Table 1 pone.0330851.t001:** Intervention core components using the COM-B model and measurement items for implementation fidelity.

COM-B constructs	Description	Measurement items
		**Stem:** My PA coach…
**Capability**	• Enhancing psychological capability to reduce barriers to engaging in PA. For example, action planning and problem solving to ensure students feel supported to be active outside of the supervised PA session • Enhancing physical capability to engage in PA. For example, demonstrating correct PA techniques and providing individualized and personalized PA considerations	“Took into account my needs and preferences” “Was knowledge about PA” “Demonstrated PA techniques (e.g., proper form) in a way that improved my confidence and capability” “Explored options with me to find something I would enjoy”
**Opportunity**	• Considering environmental and social opportunities for supporting engagement in PA – including providing a supportive and enjoyable PA environment	“Provided a supportive environment” “Helped support me to be active outside of the MoveU.HappyU sessions” “Provided an enjoyable PA experience”
		“Arranged session times that suited me”
		“Was easily contactable”
**Motivation**	• Enhancing motivation through targeting knowledge and education around the benefits of PA for mental health • Enhancing motivation through feedback and monitoring strategies such as goal setting and encouraging habit formation through prompts and cues • Eliciting positive emotions through emotional social support	“Helped my motivation for PA” “Provided me with information about things that may influence my mental health” “Was caring”
		“Was someone I liked”

*Note.* PA = physical activity; Measurement items were informed by recommendations for applying the COM-B model to physical activity intervention design and empirical evidence [41,42].

### 1:1 PA intervention delivery

The 1:1 PA intervention will be a 6-week supervised and individualized program. Participation will involve engaging in a weekly 1-h session. Each 1-h session will include: (1) 30-min of behavior change coaching; and (2) 30-min of individualized and supervised PA training. Intervention material includes a behavior change workbook for facilitating the 30-min of behavior change coaching, which has been informed by evidence-based strategies for promoting mental health through PA engagement [39]. Each week, students will complete the behavior change workbook in session with the program trainer to support the weekly learning objectives and learning experiences (see Table 2). Following completion of the 30-minute behavior change coaching, students will engage in structured and supervised PA. For a detailed description of the PA intervention protocol see [14].

**Table 2 pone.0330851.t002:** Weekly behavior change coaching learning objectives, learning experiences, and associated behavior change techniques.

Session	Behavior change techniques	Learning objectives and experiences
**Session 1: Getting started**	• Behavioral contract • Commitment • Monitoring of emotional consequences^+^	To facilitate greater awareness of current PA behavior and reasons/motives for wanting to become more physically active To affirm commitment to PA behavior change using a behavioral contract To introduce the feeling scale [44] and felt arousal scale [45] as a strategy for monitoring the emotional consequences of engaging in PA
**Session 2: Goal setting**	• Goal setting (behavior)^+^ • Action planning^+^ • Self-monitoring of behavior^+^	To become familiar with the benefits and principles of goal setting following recommendations for PA prescription and referral [46,47] To apply principles of goal setting to PA behavior change [48] To learn how to use the RPE scale [49] as a strategy to self-monitor exertion during PA and to set intensity goals (i.e., to increase or decrease intensity to reach the desired intensity range)
**Session 3: Self-talk & Self-compassion**	• Review behavior goal(s)^+^ • Discrepancy between current behavior and goal^+^ • Self-talk • Reduce negative emotions	To review behavior goals (including discussing modifying future goals) and to draw attention to any discrepancies between current behavior and the previously set goal To understand how self-talk (including inner commentary, self-statements, and thought traps) may be influencing PA progress To develop personally meaningful self-talk statements to encourage engagement in PA and to help feel good after being physically active To introduce self-compassion [50] as a strategy for managing negative self-talk and negative emotions to prevent interference with PA progress
**Session 4: Overcoming barriers to PA**	• Problem solving • Prompts/cues	To reflect on barriers to PA behavior change and problem solve solutions for overcoming barriers To introduce if-then planning [51] as a problem-solving strategy for overcoming barriers to PA behavior change To understand cues to action and personally meaningful prompt/cues (e.g., set an alarm, leave workout clothes by the door) in the environment to help facilitate PA behavior change
**Session 5: Maintaining motivation**	• Focus on past successes • Problem solving • Social support – unspecified, practical, or emotional depending on individual PA related needs	To understand personal fluctuations in motivation for PA engagement and to understand past successful strategies for maintaining current and future motivation To understand PA relapse prevention strategies and problem solve a relapse comeback plan To discuss social support as a strategy for maintaining motivation and to identify a social support network for facilitating PA engagement
**Session 6: Building on your tools**	• Problem solving	To reflect upon the strategies and tools learned throughout the intervention and to problem solve a plan for continuing to engage in PA following completion of the intervention

*Note.* PA = physical activity; RPE = rating of perceived exertion.

+ Behavior change technique reoccurs in each session.

For a detailed description of the behavior change techniques see [38].

### Group PA intervention delivery

The group PA intervention will receive the same protocol as described above though delivered in small groups of 3–8 students led by a trained Sport and Recreation PA coach. Drawing on group-dynamic principles [20,52], this number of students is ideal to help foster cohesiveness (e.g., through increased opportunity for interaction, discussion, and feedback/support from the PA coach) while reducing coordination and scheduling barriers. To promote needs satisfaction and preferences in group-based delivery, coaches will promote shared decision making on the types of activities engaged in within the group sessions.

### Control arm

Students who are assigned to the 10-week waitlist control arm will be assessed on primary and secondary outcomes at baseline (T1), at 6-weeks (T2), and at 1-month follow-up (T3). At completion of the 1-month follow-up assessment, students in the waitlist control arm will be offered the PA intervention (either group or 1:1 delivery depending on student preference). Following completion of the control arm, behavior will not be monitored or evaluated.

### Outcomes

Research outcomes to be assessed include demographic and descriptive data, primary outcomes, secondary outcomes, and implementation process evaluation outcomes.

### Demographic and descriptive data

Self-reported data to describe the characteristics of the sample will be collected including age in years, international student identification (i.e., domestic or international student), level of education (i.e., undergraduate, graduate, college program, either full-time or part-time), gender identity (i.e., women, non-binary, two-spirit, man, prefer not to answer), sexual orientation (i.e., heterosexual/straight, gay/lesbian, bisexual, pansexual, asexual, queer, two-spirit, questioning/unsure, I prefer not to answer, other), and ethnicity/race (i.e., Indigenous peoples of Canada, Indigenous outside of Canada, Arab, Black, Chinese, Filipino, Japanese, Korean, Central or South American, South Asian, Southeast Asian, West Asian, White). Students will also be asked to self-report their mental health experiences including history of mental illness using organizational structure from the DSM-5 [53], past month emotional challenges (i.e., loneliness, difficultly coping with stress in a healthy way, difficulty handling emotions, anxiety, social isolation, depression, trouble concentrating, substance use issues, unhealthy social media use), and past year mental health service use (i.e., past-year therapy or counseling, past year medication, therapy or counseling and medication use, not applicable, and other).

### Primary outcomes

**Depression.** The Patient Health Questionnaire [PHQ-9; 54] will be used. The 9-item PHQ measures the presence and severity of depressive symptoms over the past two weeks (e.g., “Feeling tired or having little energy”; “Little interest or pleasure in doing things”) ranging from 0 (*not at all*) to 3 (*nearly every day*) and aligns with the DSM-IV criteria to screen for and measure the severity of depression [54]. The total summed score ranging from 0−27 will be used in main analyses and depression symptom severity including minimal (score ranging from 5−9), minor (score ranging from 10−14), moderately severe (score ranging from 15−19) and severe (score > 20) will be calculated for descriptive purposes [54]. The PHQ-9 has high reliability and validity for screening and assessing the severity of depression and is widely used in both clinical practice and research including among post-secondary students [54–56].

**Anxiety.** The Generalized Anxiety Disorder Questionnaire [GAD-7; 57] will be used. The 7-item GAD assesses the frequency of symptoms associated with anxiety during the past two weeks (e.g., “Feeling nervous anxious or on edge”; “Trouble relaxing”) ranging from 0 (*not at all*) to 3 (*nearly every day*). The total summed score ranging from 0−21 will be used in main analyses and anxiety symptom severity including minimal (score ranging from 0−4), mild (score ranging from 5−9), moderate (score ranging from 10−14) and severe (score ranging from 15−21) will be calculated for descriptive purposes [57]. The GAD-7 is a valid and reliable measurement for assessing anxiety symptoms and the psychometric properties among young adults and post-secondary students have been demonstrated [57–59].

**Psychological distress.** The 10-item Kessler Psychological Distress Scale [K10; 60] will be used. Students will be asked to indicate how often over the last 30 days they experienced symptoms of psychological distress (e.g., “How often did you feel hopeless?”; “How often did you feel worthless?”) ranging from 1 (*none of the time*) to 5 (*all of the time*). The total summed score ranging from 10–50 will be used in analyses, with higher scores reflecting more psychological distress. Evidence of reliability and validity of the K10 has been reported among community and clinical samples [61,62] and is frequently used to monitor psychological distress among post-secondary students [63,64].

**Well-being.** The Mental Health Inventory-38 [MHI-38; 65] will be used to measure the 14-item psychological well-being subscale. Students will be asked to report how often during the past month they experienced symptoms of psychological well-being (e.g., “How much of the time, during the past month, did you feel relaxed and free from tension”; “During the past month, how much of the time have you generally enjoyed the things you do?”) on a six-point Likert scale ranging from 1 (*all of the time*) to 6 (*none of the time*). A total summed score will be used in main analyses ranging from 14–84, where higher scores represent more positive experiences of well-being. The MHI-38 has been widely used to measure well-being, and the psychometric properties have been demonstrated [66,67].

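### The scoring of the well-being primary outcome contradicts itself: the printed response codes, summed with no stated reversal, run opposite to the stated direction of the total

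*Protocol article*

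**What the plan says.** Under Primary outcomes, the well-being paragraph of the protocol article makes four statements.

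- **Instrument.** The Mental Health Inventory-38 "will be used to measure the 14-item psychological well-being subscale".
- **Item content.** Two items are shown, and both describe something good: "did you feel relaxed and free from tension" and "how much of the time have you generally enjoyed the things you do".
- **Response coding.** Items are answered "on a six-point Likert scale ranging from 1 (*all of the time*) to 6 (*none of the time". The low code therefore means most often and the high code means never.
- **Scoring and direction.** "A total summed score will be used in main analyses ranging from 14–84, where higher scores represent more positive experiences of well-being".

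The article mentions no reverse scoring for this scale. Under Allocation and blinding it says that the analyses will follow the plan set out in this paper. That section also says that the investigators, who run the statistics, are not blinded.

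In the depression paragraph of the same section, the PHQ-9 severity bands are 5–9, 10–14, 15–19, "and severe (score > 20) will be calculated for descriptive purposes". The main analyses use the 0–27 total.

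**The concern.** For a positively worded item, code 1 is the best answer and code 6 the worst. Adding such codes gives a total that rises as well-being falls, yet the article says that it rises as well-being improves. Taken together, the anchors, the sum and the stated direction do not define one score.

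The change in well-being from T1 to T2 is a primary outcome. If the printed codes were summed and the result read in the stated direction, a true improvement would be reported as deterioration, against the other three primary outcomes. The article offers adherence to its own written plan as a safeguard against bias by unblinded analysts, so that plan should not leave the direction of a primary outcome for them to settle.

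A coding slip is also easy to make here. The K10 uses the same kind of frequency answers in the opposite order, from 1 (none of the time) to 5 (all of the time).

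**Working it through.** **Inputs**, all from Primary outcomes in the protocol article unless noted: 14 items; codes 1 (all of the time) to 6 (none of the time); total 14–84; higher said to be better; planning effect d = .50 at T2 (Sample size).

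**1. Reproduce the stated range.** Minimum = 14 × 1 = 14. Maximum = 14 × 6 = 84. The stated 14–84 is reproduced.

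**2. Score response patterns both ways.** Reversing an item gives 7 − x, so the reversed total = 14 × 7 − sum = 98 − sum.

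| Answer to every item | Sum as coded | Sum after 7 − x |
|---|---|---|
| 1 (best) | 14 | 98 − 14 = 84 |
| 2 | 28 | 98 − 28 = 70 |
| 3 | 42 | 98 − 42 = 56 |
| 6 (worst) | 84 | 98 − 84 = 14 |

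As coded, the total rises as well-being worsens. After reversal it rises as well-being improves. The range is 14–84 in both columns, so the stated range cannot reveal the conflict.

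**3. Effect on the analysis.** Let Y be the sum as coded and Y* = 98 − Y. The constant 98 cancels in every change and every between-arm difference, so each group-by-time contrast in Y* is minus the same contrast in Y. Standard deviations and standard errors are equal. The sign therefore flips, while the absolute effect size, F statistic, two-sided p-value and power stay the same. A true benefit at the planning value, d = +.50, would appear as −.50.

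**4. Compare the other summed scales.** The PHQ-9, GAD-7 and K10 rise with symptom frequency. SPS-5 rises with agreement on positive items. Social Connectedness rises with disagreement (1 agree, 6 disagree) on items about lack of connection. Each matches its direction from the wording shown, with no reversal needed. Well-being is the only one that does not.

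**5. PHQ-9 bands.** A total of 0–27 has 28 possible values. The bands cover 5 (5–9) + 5 (10–14) + 5 (15–19) + 7 (21–27) = 22. The remaining 28 − 22 = 6 values, namely 0, 1, 2, 3, 4 and 20, fall in no band. The GAD-7 bands in the next paragraph (0–4, 5–9, 10–14, 15–21) cover all 22 values of 0–21.

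**The case against.** The strongest reply is that the article describes two different things: what students see on the form, and what is analysed. The direction of the analysed score is given explicitly and sensibly. Nowhere does the article say that the sum is raw or unreversed. Recoding items of a published instrument is routine, and a condensed article may leave it to scoring code. The consistent scales in step 4 need no reversal, so they do not show how the authors would report one. A wrong sign would also be conspicuous, since the total would correlate positively with the symptom scales, and it could be corrected from the item responses without loss of data.

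Most of this stands, and it limits the claim. A reader might infer that the outcome will be analysed backwards and the trial's result reversed. The article does not support that. It supports only a contradiction in the text and a risk that follows from it.

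A reader might also infer that every item should simply be recoded as 7 − response. That does not follow either. If the live form already codes 6 as all of the time and only the printed anchors are swapped, the recode would create the sign error that it was meant to prevent.

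What does not stand is that nothing needs correcting. The article goes beyond omitting a detail: it prints anchors, a sum and a direction that cannot all be true, and it names itself as the plan to be followed.

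On the PHQ-9, the reply is right that the bands are descriptive and that no student leaves any inferential analysis.

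**Conclusion.** The written scoring rule for one of the four primary outcomes is internally inconsistent and should be corrected before analysis. Summed as coded, best is 14 and worst is 84, the reverse of the stated direction. If that total were analysed and interpreted as stated, the sign of the effect would be wrong while its absolute size, p-value and power were unchanged. Whether this will happen cannot be told from the article.

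The conclusion assumes that the 12 items not shown are also positively worded, as the article's description of the subscale suggests. The inconsistency does not depend on this assumption, because the two items shown already conflict with the stated direction under the printed codes. A complete reversal of the total does depend on it.

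The PHQ-9 gap is real but minor. It affects only the descriptive severity table, where 6 of 28 possible scores have no category. Low scores are plausible in this sample, since students rating their mental health as good are eligible.

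**What to change.** 1. Check how the well-being items are coded on the REDCap form as administered.
2. If 1 is all of the time, state that the items are recoded as 7 − response before summing. If the form already codes 6 as all of the time, correct the printed anchors and do not recode.
3. Before analysis, confirm that the final well-being total correlates negatively with the PHQ-9 and K10 totals at baseline. This can be done pooled over arms, so it reveals nothing about treatment effects.
4. Restate the PHQ-9 severity bands so that they cover 0–27 without gaps or overlaps.

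The cost is a look at the form, a sentence or two in the protocol and one correlation check in the scoring code. Sample size, model and data collection do not change.

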### Objectives and hypotheses

Using a type 1 hybrid effectiveness-implementation study design [22], this three-arm parallel randomized controlled trial (RCT) will evaluate the effects of 1:1 and group-based supervised PA, compared to a 10-week waitlist control, among post-secondary students across three timepoints: baseline (T1), post-intervention (T2; 6-weeks), and follow-up (T3; 1-month post-intervention). Primary outcomes will include the immediate changes (T1–T2) in mental health indices (i.e., anxiety, depression, psychological distress, and well-being). Secondary outcomes will include changes from baseline to follow-up (T1–T3) and maintenance effects from post-intervention to follow-up (T2–T3) in mental health indices, as well changes in social well-being indices (i.e., social connectedness, social support), and PA behavior. The aims of the study include: (1) examining group differences between 1:1 PA delivery, group-based PA delivery, and the 10-week waitlist control arm on the primary and secondary outcomes; and (2) grounded in process evaluation recommendations [24], to explore implementation outcomes (i.e.,., reach, adherence, acceptability, fidelity) that may be linked to variation in primary and secondary outcomes while offering insight for wider dissemination. Based on evidence supporting various PA modalities for improving mental health [25], both 1:1 and group-based PA are hypothesized to be more effective than the waitlist control on primary and secondary outcomes, with no expected differences between the PA conditions on primary outcomes. Drawing on the social identity approach to health [20], it is hypothesized that group-based delivery will result in greater improvements in secondary outcomes including social well-being outcomes and maintenance effects compared to 1:1 delivery. However, 1:1 delivery is expected to yield more favourable implementation outcomes, due to its potential for stronger individualized support [14,26]. The results will provide novel insight into the effectiveness of different PA program delivery styles on student mental health, social well-being, and PA behaviour, while also offering implementation considerations to support the sustainability and scale-up of PA interventions across post-secondary campuses.

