### Secondary outcomes

**Social support**. The Social Provision Scale [SPS-5; 68] will be used to measure social support. The scale consists of 5-items (e.g., “I have relationships where my competence and skill are recognized”; “I feel part of a group who share my attitudes and beliefs”), on a 4-point Likert scale ranging from 1 (*strongly disagree*) to 4 (*strongly agree)*. A total summed score ranging from 5–20 will be used in main analyses, where higher scores indicate more favorable perceptions of social support. The scales validation has been shown in the general population and the post-secondary student population [68].

**Social connectedness.** The 8-item Social Connectedness Scale will be used to measure social connectedness [69]. The items portray a general emotional distance between the self and others (e.g., “I feel disconnected from the world around me”; “I don’t feel I participate with anyone or any group”) and reflect behavior, feelings, or both associated with a lack of connectedness on a 6-point Likert scale ranging from 1 (*agree*) to 6 (*disagree*). Higher scores will reflect a more reported sense of social connectedness with a potential range of 8–48. The Social Connectedness Scale displays strong psychometric properties among post-secondary students [69].

**PA behavior.** Self-reported PA behavior will be measured using the GLTEQ [70]. Students will be asked to indicate how many times on average they engaged in mild (e.g., yoga, golf), moderate (e.g., fast walking, baseball), and vigorous (e.g., running, soccer) PA for more than 15 minutes in a typical week. A common modification of assessing the average duration (in hours and minutes) per session of each intensity category of PA will be included [71–73]. Students will also be asked to report the frequency and average duration of resistance exercise (e.g., free weight, bodyweight training). Total scores for mild, moderate, and vigorous activity and resistance exercise will be calculated by multiplying self-reported times per week by average duration of sessions for each type. The scale has been used among post-secondary students [73] and has been validated for use in adult samples [70,73].

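### Well-being primary outcome: the item coding, the summed total and the stated direction conflict unless items are reversed, and no reversal is stated

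*Protocol article*

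**What the plan says.** Well-being is one of four primary outcomes. Under Objectives and hypotheses the article states: "Primary outcomes will include the immediate changes (T1–T2) in mental health indices (i.e., anxiety, depression, psychological distress, and well-being".

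Under Primary outcomes, the MHI-38 "will be used to measure the 14-item psychological well-being subscale". The two example items are "How much of the time, during the past month, did you feel relaxed and free from tension" and "During the past month, how much of the time have you generally enjoyed the things you do". Responses are given "on a six-point Likert scale ranging from 1 (*all of the time*) to 6 (*none of the time". The scoring rule is: "A total summed score will be used in main analyses ranging from 14–84, where higher scores represent more positive experiences of well-being".

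Neither that paragraph nor the Statistical analyses section mentions recoding any item before the sum is taken.

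**The concern.** Both example items are positively worded, so frequent endorsement means better well-being. The printed coding gives frequent endorsement the lowest number. A sum of those numbers falls as well-being rises, yet the article says that it rises. The three statements cannot all hold without a further step, and that step is not written down.

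What is at stake is the direction of a primary result. An analyst who applied the printed codes and summed them, and then read the result with the stated direction, would interpret a gain in well-being as a loss, in apparent conflict with any improvement on depression, anxiety and distress. The planned F-test for the group-by-time interaction does not depend on sign, so it would give no warning.

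**Working it through.** **Inputs** (Protocol article, Primary outcomes, Well-being): 14 items; codes 1 (most frequent) to 6 (least frequent); two example items, both positively worded; total 14–84; higher is said to be better.

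**1. Reproduce the stated range.**
- Raw codes: 14 × 1 = 14 to 14 × 6 = 84.
- Reversed codes (7 − x): 14 × (7 − 6) = 14 to 14 × (7 − 1) = 84.

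The range reproduces under both scorings, so it cannot show which is meant.

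**2. Check the direction, taking all 14 items as positively worded.**
- Best well-being (most frequent answer throughout): raw 14, reversed 84.
- Worst well-being: raw 84, reversed 14.
- Improvement of one category on every item: raw −14, reversed +14.

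Only the reversed total matches the stated direction.

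**3. Effect on the arm contrasts.** The sum of (7 − x) over 14 items is 14 × 7 − raw = 98 − raw. In a linear mixed model, replacing y by 98 − y multiplies every group, time and interaction coefficient by −1. Standard errors, variance components, F statistics and p-values are unchanged. In one simulated data set with 38 students per arm and all items positively worded, the arm difference was −4.55 with raw codes and +4.55 with reversed codes. In both cases |t| = 1.96 and p = 0.053. The general planning effect in the Sample size section, d = 0.50 post-intervention, would likewise read as −0.50 under the stated direction.

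**4. How far this depends on the 12 items not shown.** Let m of the 14 items be positively worded. The best possible student then has a raw sum of m × 1 + (14 − m) × 6 = 84 − 5m.

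| m | Best student's raw sum |
|---|---|
| 14 | 14 |
| 7 | 49 |
| 2 (only the items shown) | 74 |

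For any m of at least 1, the best student falls short of 84 unless the positive items are reversed, so the conflict remains. The exact inversion, with unchanged p-values, needs m = 14. With a mixture, the raw sum would partly cancel itself.

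**5. The other scales that state anchors and a direction.**

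| Scale | Item wording | Codes | Stated direction | Plain sum agrees? |
|---|---|---|---|---|
| K10 | negative | 1 least to 5 most frequent | higher = more distress | yes |
| SPS-5 | positive | 1 strongest disagreement to 4 strongest agreement | higher = more support | yes |
| Social Connectedness | negative | "ranging from 1 (*agree*) to 6 (*disagree" | higher = more connected | yes |
| Well-being (MHI-38) | positive (examples) | 1 most to 6 least frequent | higher = better | no |

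**The case against.** The strongest reply is that the article describes two different things: the response options as students see them, and the score as analysed. The direction of the analysed score is explicit and sensible. On that reading the anchors are simply in questionnaire order and a routine recode is implied. A journal article often leaves item-level scoring to a manual, an analysis plan or code. The article never says that unreversed codes are summed, and the stated range fits the recoded score equally well. The other scales show only that they need no recode, not that one has been overlooked here.

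Much of this stands. A reader might infer that the outcome is scored backwards and that a benefit will be reported as harm. The documents do not support that: it follows only if the raw codes are summed unreversed, and the article does not say that they will be. The anchors may also be a misprint. The data would not be lost in any case, since the outcome can be rescored as long as item responses are kept.

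The reply does not remove the conflict. The article is not silent on scoring: it gives the coding, the summation, the range and the direction, and these disagree. The Allocation and blinding section also commits the analyses to the plan set out in this paper, and says that the investigators involved in the analyses are not blinded. The direction of a primary outcome should therefore be settled in writing before results are seen.

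**Conclusion.** The point holds as an internal conflict in the scoring of one of four primary outcomes, and it should be corrected before analysis. The printed coding and summation give the opposite of the stated direction for items worded like the two examples, and no reversal is stated.

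The consequence is conditional. If the codes are summed as written, the sign of every arm contrast on well-being is inverted, and any count of how many primary outcomes improved is affected with it. Absolute effect size, p-values and power do not change. This exact form rests on the assumption that all 14 items are positively worded. The subscale's name and the two examples make that plausible, but the article does not show it. Whether the team intends a reversal cannot be determined from the document.

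**What to change.** Add one sentence to the well-being scoring rule: each positively worded item is recoded as 7 minus its raw code before summing, at T1, T2 and T3, so that 84 is the best well-being. If instead the anchors are misprinted and the questionnaire as administered runs the other way, correct the anchors and leave the sum alone. Check the questionnaire as administered to decide which applies, and to see whether any of the 14 items is negatively worded.

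Add one check at T1: the well-being total should correlate negatively with the PHQ-9, GAD-7 and K10 totals. A positive correlation would point to unreversed scoring. Because baseline is completed before allocation, this check reveals nothing about treatment effects.

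The cost is one sentence, one line of scoring code and three correlations. It needs no new data and no change to the sample size or the model.
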